### MBSR Analysis

Quantitative evaluation of MBSR outcomes will be conducted by comparing MBSR participants with matched control participants at selected intervals with regard to key study variables (eg, stress, burnout, and mindfulness skills). Participants enrolled in MBSR are assessed immediately before their first MBSR session and immediately after completing the final MBSR session. Matched controls are identified for each MBSR participant by randomly selecting nonenrolled individuals from the WellNurse participant pool on the basis of identical gender identity, birth year, and role (faculty, staff, and student). Controls are assessed at the same intervals as MBSR participants.

Statistical analysis will test whether MBSR participants differ significantly from controls with regard to postintervention levels of each outcome variable, controlling for preintervention levels. ANOVA models will be used to conduct initial comparisons. With time, larger samples, and thus more statistical power and more complex models (eg, multilevel modeling), can be tested to evaluate the potential impact of instructor, delivery modality (in-person vs remote), duration (1 week vs 8 weeks), and dose (number of sessions attended), as well as individual participant characteristics (eg, gender identity and role). Ongoing assessments for all WellNurse participants will allow for longer term follow-up of MBSR and control participants with regard to distal outcomes of interest (eg, academic retention). We expect significant differences between MBSR and control participants; immediate postintervention effects may be strongest, with somewhat weaker longitudinal effects observed over time. Analyses will also be able to test whether those participants who engage in ongoing mindfulness practice after formal MBSR training may experience improved outcomes as compared with those individuals who discontinue regular practice.

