### Mindfulness-Based Stress Reduction

MBSR is an 8-week experiential program including 2.5-hour weekly class sessions and a 1-day silent retreat. MBSR engages participants in simple evidence-based mindfulness practices, including meditation, mindful walking and movement, cognitive reframing, and communication strategies. Pioneered in 1979 by [name] at the University of Massachusetts Medical Center, MBSR includes didactic and experiential training that teaches participants to cultivate self-awareness by redirecting attention away from past or future concerns and focusing instead on the present moment. With regular practice, participants learn to change habitual stress reactivity patterns and instead more flexibly respond to stress with adaptive coping. As a result, participants learn to avoid internalizing stress in reactive patterns of negative emotion [35] and, thus, reduce distress and prevent negative health and mental health outcomes.

WellNurse partnered with the University of California San Diego School of Medicine Center on Mindfulness and Brown University Mindfulness Center to provide remote, 8-week MBSR courses via Zoom and intensive week-long, in-person MBSR courses. MBSR was offered as an elective course to count toward the students’ elective requirements for Nursing. Additionally, faculty and staff were provided work time to participate in the program. Selected WellNurse project personnel including faculty, staff, and graduate students completed a multiyear teacher training certification process through the University of California San Diego and Brown University Mindfulness Center to develop a group of certified MBSR teachers to support long-term project sustainability.

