## Results

### Overview

The project was funded on January 1, 2022. Data collection started in March 2022. A total of 267 participants have been recruited. Results will be published after each semester starting in December 2023.

The primary study variables will be analyzed 4 times per year to track population outcomes and changes. Regression analysis will be conducted to examine the relationship of students’ on-time progression, stress, resilience, and burnout with physical and emotional health variables and on-time progression. Subanalysis will be conducted for unique groups such as first and fourth year students, faculty and staff, and graduate students, as well as students from historically underrepresented populations such as first-generation college students and racial and ethnic minorities. Additionally, program retention, on-time graduation, and faculty and staff retention will be tracked over time. The cost of implementing MBSR, massage therapy, MasterChef, and fitness events will be tracked to determine cost per student. Additionally, feasibility will be measured using qualitative focus group interviews with students who complete specific interventions along with attrition rates for completing specific interventions such as MBSR and MasterChef.

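### The immediate MBSR post-assessment is timed by reaching the last session, so course leavers have no described immediate outcome and the comparison with controls is at risk of completer bias

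*Protocol article*

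**What the plan says.** All references are to the protocol article.

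- **MBSR participants (MBSR Analysis):** "Participants enrolled in MBSR are assessed immediately before their first MBSR session and immediately after completing the final MBSR session".
- **Controls (MBSR Analysis):** "Controls are assessed at the same intervals as MBSR participants". They are chosen by "randomly selecting nonenrolled individuals from the WellNurse participant pool on the basis of identical gender identity, birth year, and role".
- **Analysis (MBSR Analysis):** the groups are compared on "postintervention levels of each outcome variable, controlling for preintervention levels", for "key study variables (eg, stress, burnout, and mindfulness skills"). A later model is to examine "dose (number of sessions attended").
- **Course (Mindfulness-Based Stress Reduction, among the interventions):** "MBSR is an 8-week experiential program including 2.5-hour weekly class sessions and a 1-day silent retreat". An intensive one-week format is also offered.
- **Attrition (Results, Overview):** feasibility will be judged in part by "attrition rates for completing specific interventions such as MBSR and MasterChef". No rate is given.
- **Other data on leavers (Comprehensive Wellness Survey):** all participants are surveyed in weeks 4 and 14 of the fall and spring semesters, including perceived stress, burnout and resilience. The mindfulness and affect questionnaires are listed only as extra pre and post measures for people who sign up for MBSR.

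**The concern.** The trigger for the MBSR post-assessment is an event that only people still in the course reach. The control assessment cannot carry such a condition. Followed as written, the rule lets the MBSR group be filtered by persistence while the control group is not.

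Baseline adjustment deals with leavers who differed at the start. It does not deal with leavers whose stress developed differently afterwards. That is plausible here, because the Comprehensive Wellness Survey section says examinations and competency tests start around the third to fourth week and raise stress.

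The affected comparison matters. MBSR Analysis expects the immediate effects to be the strongest, and Principal Findings says interventions shown to work will enter the standard curriculum. Early leavers are also the low-attendance people whom the dose model needs. Immediate measurements that were never taken cannot be recovered by any later analysis plan.

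**Working it through.** The article states no sample size, effect size or drop-out figure for MBSR, so there is no plan figure to reproduce. The check has two parts.

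**1. What each group is described as providing**

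| | Immediate post-assessment | Described fallback |
|---|---|---|
| MBSR, reaches last session (even with missed sessions) | Yes | Not needed |
| MBSR, leaves before last session | None described | Week 14 survey for stress, burnout, resilience; none for mindfulness and affect |
| Control | Same interval, no completion condition | Week 14 survey, as for all participants |

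Week 14 need not coincide with the end of a course, least of all a one-week course.

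**2. Illustrative size, true effect zero**

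Let p be the fraction leaving and g the gap in baseline-adjusted outcome, leavers minus stayers (higher = worse). The mean for all starters equals the stayers' mean plus p × g. Using stayers only therefore shifts the result by p × g towards MBSR.

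Assumed p of 0.10 to 0.30 and g of 0.3 to 0.7 SD give:
- lowest: 0.10 × 0.3 = 0.03 SD
- middle: 0.20 × 0.5 = 0.10 SD
- highest: 0.30 × 0.7 = 0.21 SD

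A second route assumes a pre-post correlation of 0.6, so the residual SD is √(1 − 0.6²) = 0.8. Leaving has correlation r with a worse-than-predicted change. The shift is then r × 0.8 × φ(z)/(1 − p), where z is the (1 − p) normal quantile and φ the normal density. At p = 0.20, z = 0.842 and φ(z) = 0.280, so φ(z)/(1 − p) = 0.350:
- r = 0.3: 0.3 × 0.8 × 0.350 = 0.084 SD
- r = 0.5: 0.5 × 0.8 × 0.350 = 0.140 SD

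A simulation with 400,000 people per group and baseline adjustment agrees. Entries are SD; positive favours MBSR.

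| Reason for leaving | 10% | 20% | 30% | 40% |
|---|---|---|---|---|
| Random, or baseline only | 0 | 0 | 0 | 0 |
| Worse change, r = 0.3 | 0.046 | 0.083 | 0.118 | 0.154 |
| Worse change, r = 0.5 | 0.078 | 0.141 | 0.198 | 0.255 |
| Better change, r = −0.3 | −0.049 | −0.082 | −0.118 | −0.151 |

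The zeros are within 0.003 SD. With every starter assessed, the error stayed within 0.005 SD in all scenarios. Dropping each leaver's matched control did not help: at 20% and r = 0.3 the shift was 0.083 SD either way, because the controls were not matched on persistence or trajectory.

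**A separate effect.** Suppose leaving is random, finishers gain 0.30 SD and leavers gain nothing. Finishers show 0.30 SD, while the average over all starters is 0.30 × (1 − p): 0.27, 0.24, 0.21 and 0.18 SD at 10%, 20%, 30% and 40% leaving. The finisher figure then overstates what offering MBSR achieves.

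**The case against.** **Leavers are not without data.** A reader might infer that they have no outcome at all. The documents do not support that: the week 14 survey still reaches them for stress, burnout and resilience. This stands, and it narrows the gap to the immediate comparison and to mindfulness and affect.

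**The sentence may only state timing.** It does not say that leavers are excluded or not contacted, someone who misses sessions but attends the last one is assessed, and a dose model presupposes varied attendance. This is fair. One should not conclude that most low-attendance people are lost. But the text still describes no immediate assessment for someone who has stopped, and the same change of wording settles either reading.

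**The direction is not proven.** The bias vanishes if leaving is random or depends only on baseline, and it reverses if improvers leave. Course credit, work time for faculty and staff, and the one-week format may all limit stress-driven leaving. Controls may also fail to respond. If 20% of enrollees and 10% of controls are missing, each with a 0.5 SD gap, the net shift is 0.20 × 0.5 − 0.10 × 0.5 = 0.05 SD rather than 0.10 SD. All of this stands.

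**A condensed article leaves analysis detail elsewhere.** True of analysis sets and missing-data handling, and their absence is not the point here. The timing of data collection is stated in the article.

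**Conclusion.** The point holds in limited form. As written, the rule gives course leavers no described immediate post-course assessment, while controls face no completion condition. This creates a risk of completer bias in the immediate MBSR comparison, most clearly for mindfulness and affect, where nothing else is described.

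A reader might go further and say that the comparison favours MBSR. That is probable if people leave because things are getting worse, but the documents give neither an attrition rate nor reasons for leaving, so neither sign nor size is established. Under assumed leaving of 10% to 30%, the illustrative range is 0 to about 0.2 SD towards MBSR, with up to about 0.12 SD the other way if improvers leave (r = −0.3). These figures rest on the assumed leaving rates, gaps and correlations, and on complete response among controls. Confidence is high on the asymmetry of the rule and moderate on direction.

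**What to change.** Reword MBSR Analysis along these lines: everyone who attended the first MBSR session is sent the post-assessment on the end date of their course, whether or not they are still attending, and their matched controls are assessed on the same date.

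Alongside this:
- make the main MBSR comparison by enrollment;
- use sessions attended only in the dose model;
- report post-assessment non-response in both groups.

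The cost is a sentence in the plan, a survey link and reminders to people who have stopped attending. Some leavers will not respond, so the risk is reduced rather than removed, and the estimated effect will probably be smaller. No additional participants are needed.

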### Measures

#### Comprehensive Wellness Survey

After completing a web-based consent form, participants complete a comprehensive health behavior survey. This survey is distributed during week 4 and again during week 14 (the week before finals week) in the fall and spring semesters. Week 4 was selected based on the typical nursing student’s academic loads and stress. Examinations and competency testing begin each semester’s third to fourth week, accelerating stress during those periods. Participants complete the comprehensive health behavior survey during designated class or work time. Additional measures are collected before specific engagement in targeted study interventions. Participants’ answers are tracked through the project using unique ID codes. As listed below, several variables are assessed to capture the health of nursing students. The comprehensive measurement strategy aligns with Priority Area 2 from the National Academy of Sciences [8], which recommends the longitudinal use of valid and reliable measurements of burnout and factors that mitigate burnout to drive effective interventions and data-driven decision-making at the organizational level.

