#### Mindfulness-Based Stress Reduction

Participants who sign up to participate in MBSR complete additional pre- and postintervention measures.

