### Comparisons With Prior Work

#### WellNurse Room

Effective strategies to promote resilience and reduce burnout require system and environmental interventions [43]. The room contains floral murals, live plants, aromatherapy, meditation cushions, light therapy, coloring books, and tactile engagement. The WellNurse room is stocked with meditation cushions and a massage therapy table. Weekly mindfulness sessions are offered to support MBSR practices. A licensed massage therapist provides complimentary massage therapy in 15- to 30-minute sessions. Aromatherapy and massage therapy have shown stress-reducing effects [44,45]. This study aims to understand how environmental changes may influence nursing students’ resilience, stress, and well-being.

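### MBSR matching and adjustment leave out program level and year, give retention no baseline control, and put faculty and staff matches at risk by requiring an identical birth year

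*Protocol article*

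**What the plan says.** Results, MBSR Analysis, sets the control rule: controls come from "randomly selecting nonenrolled individuals from the WellNurse participant pool on the basis of identical gender identity, birth year, and role (faculty, staff, and student". The same section says that "Controls are assessed at the same intervals as MBSR participants", and that the test compares "postintervention levels of each outcome variable, controlling for preintervention levels". It adds that "ANOVA models will be used to conduct initial comparisons"; richer models may follow as numbers grow, with gender identity and role as the examples of individual characteristics. It also plans longer follow-up of both groups on distal outcomes, with academic retention as the example.

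Entry to MBSR is by choice. Under Measures, Mindfulness-Based Stress Reduction: "Participants who sign up to participate in MBSR complete additional pre- and postintervention measures". Under the intervention heading of the same name, "MBSR was offered as an elective course" for students, and faculty and staff could attend in work time.

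Baseline data exist for the wider pool. Of the comprehensive survey, which includes stress, burnout and resilience, Methods says: "This survey is distributed during week 4 and again during week 14".

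Elsewhere the article treats program stage as important. Results, Overview, plans subanalyses for first-year, fourth-year and graduate students. Results, MasterChef Analysis, matches controls on gender, ethnicity and year in college. The Discussion section on MBSR includes faculty and staff in the aim.

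**The concern.** In a comparison that people enter by sign-up, the matching variables and covariates carry the whole burden of making the groups alike. Three things look weak here.

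- One student role covers first-year undergraduates through graduate students. Program stage plausibly affects stress, workload, room for an elective and the chance of progressing on time. It is used for MasterChef but not for MBSR.
- Adjusting an outcome for its own earlier value works for stress, burnout and mindfulness. It cannot work for retention, which has no earlier value. For that outcome only gender, birth year and role remain.
- An identical birth year is easy to meet among students close in age and hard to meet in a small group whose ages are widely spread. Faculty and staff without a match would drop out of the comparison, and the result would lean towards students.

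The stake is how the MBSR result can be read. The article says that effective interventions will enter the standard curriculum.

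**Working it through.** The article states no sample size, match rate or effect size for the MBSR comparison, so there is no figure of its own to reproduce. Three checks apply.

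**1. Which variables are controlled**

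| Analysis | Matched on | Stated covariate |
|---|---|---|
| MBSR, stress, burnout, mindfulness | gender identity, birth year, role | own preintervention level |
| MBSR, retention | gender identity, birth year, role | none possible of that kind |
| MasterChef | gender, ethnicity, year in college | baseline, by repeated measures |

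Program level and year are missing from both MBSR rows.

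**2. Chance that a faculty or staff enrollee has an identical control**

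From the article: 267 participants over all roles. Assumed, because the article does not say: 20 to 80 faculty and staff, split evenly between the two roles; 88% of one gender; birth years spread evenly over Y = 30 or 40 years; 20% or 40% enrolled in MBSR. Let n be the nonenrolled faculty and staff. A given control matches an enrollee of the majority gender with probability 0.88/(2Y), and one of the minority gender with probability 0.12/(2Y). If controls may be reused, the matched share is

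0.88 × [1 − (1 − 0.88/(2Y))^n] + 0.12 × [1 − (1 − 0.12/(2Y))^n].

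- Lowest case: 20 people, 40% enrolled, n = 12, Y = 40. 0.88 × [1 − 0.989^12] + 0.12 × [1 − 0.9985^12] = 0.109 + 0.002 = 0.11.
- Highest case: 80 people, 20% enrolled, n = 64, Y = 30. 0.88 × [1 − 0.98533^64] + 0.12 × [1 − 0.998^64] = 0.538 + 0.014 = 0.55.

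Simulation under the same assumptions, with and without reuse of controls, gives:

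| Faculty and staff in pool | Share of enrollees matched |
|---|---|
| 20 | 11–19% |
| 40 | 19–33% |
| 60 | 27–46% |
| 80 | 33–55% |

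For students (187 to 247 in the pool, 80% within five birth years and the rest spread over 20, 10% to 40% enrolled), 85% to 96% are matched.

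**3. What adjustment for the baseline score leaves behind**

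Suppose enrollees differ from controls by d SD in a stable true level of stress, and the baseline score has reliability r. Without adjustment the bias is d. With adjustment it is d × (1 − r). Neither d nor r is given in the article; both are assumed.

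| d | r = 0.7 | r = 0.8 | r = 0.9 |
|---|---|---|---|
| 0.2 | 0.06 | 0.04 | 0.02 |
| 0.5 | 0.15 | 0.10 | 0.05 |

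So the planned adjustment removes 70% to 90% of such an imbalance. This covers selection on that one score only. It says nothing about differences in program stage or motivation, and nothing about retention.

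**The case against.** The strongest reply is that the analysis already handles the obvious confounder. Each outcome is adjusted for its own value taken just before the first session, with controls measured at the same times. This stands. A reader who sees only the matching rule might infer that self-selection is uncontrolled, and the same section of the article contradicts that. Matching on baseline stress as well is optional. If people sign up on the stress that the survey records, the leftover bias shrinks towards zero. If enrollees are truly more stressed, the leftover makes MBSR look less effective, not more.

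A reader might also infer that many faculty and staff will go unmatched, so that the effect is estimated almost only in students. The article does not show this. It gives neither the role split nor the age spread, and recruitment continues through December 2024, so the pool is not fixed at 267. A rule for unmatched participants may stand in the full protocol or analysis plan. The loss is a risk, though a sizeable one in every scenario tried.

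Birth year also stands in partly for program stage, since a pair must be the same age. That holds only in part: it does not separate an older undergraduate from a graduate student born in the same year.

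Finally, it is tempting to say that controls' attendance at other activities is ignored, given that "Weekly mindfulness sessions are offered to support MBSR practices" and that sign-in is recorded. The article is silent on how those records will be used, and silence is not exclusion. Nor does the article leave out participant characteristics altogether: later models may include them, with gender identity and role only as examples.

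**Conclusion.** The concern holds in a limited form. Self-selection into MBSR is incompletely controlled. Program level and year are absent from the stated matching and covariates, which is out of step with the article's own MasterChef matching and planned subanalyses. For academic retention, the matching is the only stated control. These points rest on the text alone.

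The faculty and staff point is a risk whose size depends on assumptions. With 20 to 80 of them in a pool of 267, and the age, gender and enrollment mix assumed above, about 11% to 55% of those enrolled would have an identical control, so about 45% to 89% would not. The residual bias of 0.02 to 0.15 SD in stress or burnout is likewise conditional on assumed imbalance and reliability. It does not by itself discredit the comparison.

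The change is worth making but does not call for a new design.

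**What to change.** In MBSR Analysis:

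- Replace identical birth year with an age caliper, keeping gender identity and role.
- Add program level and year for students, in the matching or in the model.
- Include baseline stress, burnout and resilience as covariates, above all for retention. Use only survey values that predate the class start: the article does not give class dates, so a week-4 value may fall after the first session. GPA can be added for students only.
- Draw each class's controls from people not enrolled in MBSR at that class's start date.
- Say that the model adjusting for the preintervention level is an analysis of covariance, since the article says only ANOVA.

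A full propensity-score redesign is not needed. The survey items are already collected, and year and graduate status are needed for the planned subanalyses anyway. The cost is a changed matching procedure, slightly looser age matching and reliance on completed pre-class surveys. For classes already run, newly chosen controls may lack the measures taken at class-specific times, so the change is cleanest for future classes.

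### The initial MBSR comparison names no class term although MBSR is taught in classes, so its standard error is likely too small by an unstated amount; leaving out the matching works the other way

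*Protocol article*

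**What the plan says.** The MBSR Analysis section states the target of the test as "postintervention levels of each outcome variable, controlling for preintervention levels", MBSR participants against controls. The next sentence gives the model: "ANOVA models will be used to conduct initial comparisons". Neither class nor matched set is named as a term.

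The same paragraph then postpones richer models: "With time, larger samples, and thus more statistical power and more complex models (eg, multilevel modeling), can be tested". Their stated purpose is to "evaluate the potential impact of instructor, delivery modality (in-person vs remote), duration (1 week vs 8 weeks), and dose", together with participant characteristics.

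The intervention section on Mindfulness-Based Stress Reduction shows that delivery is in groups: "MBSR is an 8-week experiential program including 2.5-hour weekly class sessions and a 1-day silent retreat". The project's partners "provide remote, 8-week MBSR courses via Zoom and intensive week-long, in-person MBSR courses". Controls are chosen one by one: "Matched controls are identified for each MBSR participant by randomly selecting nonenrolled individuals from the WellNurse participant pool", with identical gender identity, birth year and role.

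**The concern.** People taught together share an instructor, a group and a calendar period, so their outcomes after the course may be correlated. Controls share no MBSR class, so this correlation arises in one arm only. An ANOVA without a class term counts every MBSR participant as an independent observation and, if the class correlation is positive, understates the variance of the group difference.

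The deferral does not solve this. The later models answer other questions, and the first test stands without them. The article itself lists instructor as a possible influence, so it recognises a source of within-class correlation that the first test leaves out.

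The early results matter. The article plans publication after each semester, a rapid-cycle process that can alter interventions, and a standard curriculum built from the interventions that show effectiveness. An early MBSR result with too narrow an interval could feed all three.

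**Working it through.** **Inputs.** From the article: ANOVA for the first comparison, group classes, individually matched controls. The article gives no number of MBSR participants, study participants per class (m), number of classes (k), class correlation (ICC), matching ratio or within-pair correlation (r). A 5% level is stated only under MasterChef Analysis; I assume it for MBSR, two-sided. I also assume 1:1 matching, equal total variance in both arms, and controls uncorrelated with one another. The article states no power or type I error for MBSR, so there is no figure to reproduce.

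**Formula.** With n per arm and residual variance s², ANOVA takes the variance of the difference as 2s²/n. The true variance is (s²/n) × {[1 + (m − 1)ICC] + 1 − 2r}. The ratio of true to assumed variance is

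V = 1 + (m − 1)ICC/2 − r,

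and the true size of a nominal 5% test is 2[1 − Φ(1.96/√V)].

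**Step 1: class ignored, no within-pair correlation (r = 0).**
- m = 15, ICC = 0.05: V = 1 + 14 × 0.05/2 = 1.35, size 9.2%.
- m = 20, ICC = 0.10: V = 1 + 19 × 0.10/2 = 1.95, size about 16%.

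| m | ICC 0.01 | ICC 0.05 | ICC 0.10 |
|---|---|---|---|
| 10 | 5.5% | 7.7% | 10.4% |
| 15 | 5.8% | 9.2% | 13.3% |
| 20 | 6.1% | 10.7% | 16% |

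Over a wider range, m = 8 with ICC 0.01 gives 5.4%, and m = 30 with ICC 0.15 gives 27.1%. If few study participants sit in each class the effect is small: at ICC 0.05, m = 5 gives V = 1.10 and about 6.2%, and m = 3 gives V = 1.05 and about 5.6%.

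**Step 2: matching ignored, no class effect.** Here V = 1 − r. The size is 4.4% (r = 0.05), 3.9% (r = 0.1), 2.8% (r = 0.2) and 1.9% (r = 0.3). The test is conservative and loses power.

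**Step 3: both ignored, r = 0.2.**

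| m | ICC 0.01 | ICC 0.05 | ICC 0.10 |
|---|---|---|---|
| 10 | 3.3% | 5.3% | 8.0% |
| 15 | 3.6% | 6.8% | about 11% |
| 20 | 3.8% | 8.3% | 13.8% |

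The two effects cancel when r = (m − 1)ICC/2. That is 0.095 at m = 20, ICC 0.01; 0.35 at m = 15, ICC 0.05; and 0.95 at m = 20, ICC 0.10.

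**Step 4: simulation.** Baseline-adjusted ANOVA was simulated with a pre-post correlation of 0.5 and 4,000 runs per scenario. At a true size of 5% the simulation error is √(0.05 × 0.95/4000), about 0.3 percentage points. Four classes of 20 with r = 0 gave 10.9% at ICC 0.05 and 15.6% at ICC 0.10. With r = 0.2 these became 8.7% and 14.6%. Matching alone at r = 0.2 gave 2.8% to 3.2% across the layouts. This agrees with the formula.

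**Step 5: a test that respects both structures.** Matched differences in residual outcome were averaged within class, and the class means were tested on k − 1 degrees of freedom. For 4 classes of 15, 4 of 20 and 6 of 10, at ICC 0.05 with r = 0 and ICC 0.10 with r = 0.2, the simulated size was 4.5% to 5.1%.

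**The case against.** **A reader might infer that the test runs well above 5%, and that ignoring both class and matching causes this.** The documents do not support either part. Ignoring positive within-pair correlation overstates the variance, so it lowers the size. How far class pushes the size up depends on m and ICC, which are not stated. The relevant m is study participants per class, and the article does not say how many sat in each of the partners' courses. Within the assumed ranges the net size runs from below nominal to clearly inflated.

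**A reader might also infer that ANOVA fails to deliver the baseline adjustment.** It does not follow. The sentence before the model states that preintervention levels are controlled for, so the two sentences together describe a baseline-adjusted analysis in loose wording.

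**The article is condensed.** ANOVA models, in the plural, could include blocked or nested forms, and error terms are often left to a fuller plan. This has some weight and is a reason for moderate confidence. But the article does address multilevel modelling, and it assigns it to a later stage and to other questions.

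**Few classes.** With one class, class and MBSR effects cannot be separated by any model. With two or three, a random class variance is poorly estimated. This stands and shapes the fix. It does not justify a test that assumes independence: even when the class variance cannot be estimated, the uncertainty it adds remains.

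**Conclusion.** The point holds in limited form. As written, the first MBSR comparison does not account for class clustering in one arm, and the deferred models are not directed at correcting that. With positive class correlation and negligible within-pair correlation, the true size is about 5.5% to 16% for 10 to 20 study participants per class and ICC 0.01 to 0.10. Those inputs, the 1:1 ratio and the two-sided 5% level are assumptions. Omitting the matching pulls the size down and can offset the inflation wholly when classes are small or the ICC low, but only in part at the upper end. The net direction therefore cannot be fixed from the article. What can be said is that the stated analysis does not match the design in either respect, and that relying on two errors to cancel is not a sound basis for the first published MBSR result. It should be corrected; confidence is moderate.

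**What to change.** From the first comparison:

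- Keep the stated preintervention adjustment, with the pre score as covariate.
- Fit a partially nested model: a fixed MBSR-versus-control effect, a random class effect in the MBSR arm only, a matched-set term, and small-sample degrees of freedom such as Kenward-Roger.
- When classes are few, use instead a test on class means of the matched differences in baseline-adjusted outcome, with k − 1 degrees of freedom for k classes.
- Where only one class has run, report the comparison as descriptive and say why.
- State the significance level and sidedness for MBSR.
- Record class membership for each MBSR participant. The planned instructor, format and attendance analyses imply that much of this is held, but the article does not say so.

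The multilevel analyses of instructor, modality, duration and dose can stay as a later step. The change is one of analysis wording plus, at most, one recorded variable. The price is wider intervals and little power until several classes have run.
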